#### 3.7.3. Visit 3 (Follow-Up Visit)

Patients will undergo to the same procedures as previously described: clinical evaluation; photographic documentation; EORTC QLQ-C30, EORTC QLQ-H&N35, EQ-5D-5L questionnaires, pain evaluation with VAS score and blood samples as per normal clinical practice and CD8 and CD16 dosages.

#### 3.7.4. Visit 4 (Follow-Up Visit)

The patients will undergo clinical evaluation; photographic documentation; evaluation treatment response according to RECIST criteria (version 1.1); CT, MRI or PET-CT (same imaging as pre-operative evaluation); photographic documentation; EORTC QLQ-C30, EORTC QLQ-H&N35, EQ-5D-5L questionnaires, pain evaluation with VAS score, blood samples as for normal clinical practice and CD8 and CD16 dosages.

Biopsy will be performed only in the case of clinical evidence or radiologic suspect.

#### 3.7.5. Visits 5 and 7 (Follow-Up Visit)

The patients will undergo the same procedures as previously described for visit 3.

#### 3.7.6. Visits 6, 8 and 9 (Follow-Up Visit)

The patients will undergo the same procedures as previously described for visit 4

### 3.8. Description of Sample Size Calculation

Sample size estimation was done by using the superiority hypothesis in two independent parallel sample proportions [28,29,30,31,32,33,34]. Primary endpoint is the evaluation of the objective OR tumor response (CR + PR) based on RECIST criteria between treatment and control arm. According to literature data, treatments with cetuximab determine an OR response rate of about 36%.

We assume that ECT can provide an increase of about 20% of the OR (the EURECA study reports a global H&N response rate of 56% in recurrent, mucosal head and neck tumors).

The test statistic used is the one-sided T-test. The significance level of the test was targeted at 0.15. Group sample sizes of 48 in group one and 48 in group two achieve 81% power to detect a difference between the group proportions of 0.2000. The proportion in group one (the treatment group) is assumed to be 0.36 under the null hypothesis and 0.56 under the alternative hypothesis. The proportion in group two (the control group) is 0.36. The significance level actually achieved by this design is 0.16.

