#### ECT Procedure

Cliniporator™ (IGEA S.p.A., Italy) will be used to deliver electric voltage with the following parameters: 8–96 pulses of 140–1000 V, of 100 μs duration, at 5000 Hz repetition frequency. The electrodes will be chosen between linear, hexagonal, finger and expandable deployable endoscopic ones depending on the size and tumor localization. Generally, linear needle electrodes will be used to treat cutaneous, lymph node and subcutaneous lesions smaller than 3 cm while use of the hexagonal will be limited in wider tumors. Finger and expandable deployable endoscopic electrodes will be used to reach less accessible lesions, such as those localized in the oro-pharynx (tonsil and base of tongue). The surgeon will perform multiple procedures of the electrode in the tumor tissue covering the complete area of the lesion to be treated and possibly a margin area of free tissue growths of 3–5mm (overtreatment) around the lesion itself. The procedure can require one or more electrode insertion and pulse applications and must be completed within 40 min from the end of bleomycin injection.

If the procedure will be performed under local anesthesia, the last will be induced between bleomycin injection and the beginning of the electrode’s insertion; while if the procedure will be performed under general anesthesia, bleomycin injection will follow the induction of anesthesia itself.

The patients will be randomized 1:1 to ECT or standard treatment.

In Figure 1 the treatment in the two arms of treatment is schematically represented.

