### 3.7. Description of Study Procedures

#### 3.7.1. Visit 1

Patients must sign individual informed consent form before they undergo any study procedures. Patients who fulfil all inclusion criteria and do not meet any exclusion criteria will be enrolled.

At Visit 1, patients will be interviewed and their study eligibility determined according to the inclusion and exclusion criteria and then will be randomized 1:1 to ECT or standard treatment. The investigator will collect and document the patient’s medical history with special emphasis on oncology history, previous chemotherapy, and response to prior therapy. Patients will be asked about concomitant treatments, medications, and events at each patient contact and each visit. Treatment information will include nature of treatment, start date, end date, and reason for treatment. Drug information gathered and documented will include dose, route of administration, frequency, start date, end date, and indication, as applicable. Continuation and discontinuation of treatments and drugs will be verified with the patient at each visit.

The patient will undergo a comprehensive physical examination that includes weight, height, and vital signs. Patients observed with an active infection of any kind will be excluded from study participation.

The ECOG (Eastern Cooperative Oncology Group) Performance Status [27] will be evaluated as inclusion criteria: patients who are grades 0, 1 or 2 are eligible for study participation.

CBC and coagulation profiles will be measured at the enrolment visit (Visit 1). Patients with an absolute neutrophil count below 1000/mL, platelet count below 70,000/mL, and/or INR above 1.5 will be excluded from study participation.

Pain will be assessed at all visits using a 100 mm anchored visual analogy scale with 0 being “No Pain” and 100 mm being “Pain as bad as it could possibly be.”

EORTC QLQ-C30, EORTC QLQ-H&N35, EQ5d questionnaires, will be completed at each follow up visit to measure the patient’s quality of life.

All patients will undergo pre-anesthesia assessment in accordance with the usual and customary anesthesia assessment procedures at the clinical site. Patients found not to be acceptable for either general anesthesia or monitored anesthesia care (conscious sedation) will be excluded from study participation.

#### 3.7.2. Visit 2

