### 3.9. Statistical Analysis

Continuous variables will be presented as mean ± standard deviation if normally distributed; as median and interquartile range (IQR) if not normally distributed. The difference between follow-up values and baseline values will be computed and the null hypothesis (no effect on local disease control and quality of life or pain) will be tested by two-sided Student’s t-test (if differences normally distributed) or by Mann–Whitney test (if differences not normally distributed). ANOVA test (normally distributed variables) or Kruskall–Wallis test (non-normally distributed variables) will be used to test the null hypothesis by adjusting for proper covariates. For categorical variables, the chi square test for multiple comparisons will be used.

The objective response will be reported as a categorical variable and marked as a response rate.

Survival analysis will be performed with the Kaplan–Meier test, and the difference between the curves with the log-rank test.

Quality of life and pain assessment will be evaluated as continuous variables. The difference between the follow-up values and baseline values will be calculated and the null hypothesis (no effect) will be tested with two-tailed Student’s t-test (if the differences are distributed according to a normal one) or with the Mann–Whitney test (if the differences are not distributed according to a normal). The ANOVA test will be used to verify the null hypothesis by adjusting for appropriate covariates (if the differences are distributed according to a normal one) or with the Kruskal–Wallis test.

Differences will be considered significant at *p* < 0.05.

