## Figures and Tables

**Figure 1 cancers-13-02210-f001:**
[figure not shown]
Trial design flowchart.

**Table 1 cancers-13-02210-t001:** Inclusion and exclusion criteria.

Inclusion Criteria	Exclusion Criteria
Age ≥ 18 years	Age < 18 years
Progressive disease (single recurrence on T and N0) of oral cavity or oropharynx. Absence of other systemic metastases in any site outside the locoregional recurrence	Other symptomatic lesions not under control
Histological diagnosis of squamous cell carcinoma	Lesions not suitable for ECT (bone invasion, large vessels infiltration, etc.)
Measurable lesions suitable for application of electric pulses	Lesions not eligible for systemic treatment with cetuximab + platinum + 5-fluorouracil therapy
Performance status (Karnofsky ≥ 70; WHO ≤ 2)	Acute lung infection
Life expectancy> 3 months	Symptoms of poor lung function
Ability to understand the information given and sign informed consent	Non-correctable severe coagulation disorders
Patients must have offered standard treatments	Previous allergic reactions to bleomycin
	Previous cumulative dose of 250 mg/m^2^ of bleomycin exceeded
	Chronic renal dysfunction (creatinine> 150 µmol/L must be considered a lower administered dose of bleomycin)

**Table 2 cancers-13-02210-t002:** Visits scheme.

Visit		1	2		3	4	5	6	7	8	9
Time		Month -1 (up to 1 month prior the treatment)	Month 0		Month 1 ± 1 week	Month 2 ± 1 week	Month 4 ± 1 week	Month 6 ± 1 week	Month 8 ± 1 week	Month 10 ± 1 week	Month 12 ± 1 week
	Visit Description	Restaging, enrolment, randomization	Day of treatment Control group: cetuximab + platinum + 5- fluorouracil Treatment group: electrochemotherapy	Post treatment evaluation (discharge day ± 1 week)	Follow up visit	Follow up visit Cut off time to evaluate treatment response	Follow up visit	Follow up visit	Follow up visit	Follow up visit	Follow up visit
Type of assessment											
Clinical evaluation			X	X	X	X	X	X	X	X	X
Duration of hospitalization				X							
CT, MRI or PET-CT		X	Estimation of Lesion size and assignment of T stage			X		X			X
Identification of the target lesion		X	X	X							
Photographic documentation		X	X		X	X	X	X	X	X	X
EORTC QLQ-C30, EORTC QLQ-H&N35, EQ-5D-5L questionnaires		X		X	X	X	X	X	X	X	X
Pain evaluation with VAS score		X		X	X	X	X	X	X	X	X
Blood samples as per normal clinical practice		X	X		X	X	X	X	X	X	X
CD8 and CD16 dosage			X		X	X	X	X			
Recording of the drugs for pain control				X		X	X	X	X	X	X
Recording of concomitant treatment					X	X	X	X	X	X	X

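### The only tests named for the primary response comparison are unadjusted; prespecifying adjustment for baseline lesion size and ECOG could add a little power at no cost in patients

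*Protocol article*

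**What the plan says.** **Endpoint and test.** Section 3.8 defines the endpoint: "Primary endpoint is the evaluation of the objective OR tumor response (CR + PR) based on RECIST criteria between treatment and control arm". The design basis is "Sample size estimation was done by using the superiority hypothesis in two independent parallel sample proportions", and the test is given as "The test statistic used is the one-sided T-test". On the level: "The significance level of the test was targeted at 0.15". With 48 patients per arm and response rates of 0.56 and 0.36, the section reports 81% power and an achieved level of 0.16.

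**Analysis section.** Section 3.9 treats objective response as categorical and says: "For categorical variables, the chi square test for multiple comparisons will be used". It plans adjustment for unnamed covariates through ANOVA or Kruskal-Wallis, in the setting of differences between follow-up and baseline values. The null hypothesis given there mentions local disease control alongside quality of life and pain. It closes with a general significance threshold of p < 0.05.

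**Baseline data.** Table 2 (visits scheme) places imaging and ECOG status at Visit 1. Its imaging row carries the entry "Estimation of Lesion size and assignment of T stage" on the day of treatment. Section 3.7.1 sets the ECOG range: "patients who are grades 0, 1 or 2 are eligible for study participation". Under ECT Procedure, the electrode type is chosen "depending on the size and tumor localization".

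**Allocation.** Randomisation is 1:1 at Visit 1. The article names no stratification factor.

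**The concern.** Patients with larger tumours or poorer performance status may respond less often under either treatment. If so, an analysis that ignores these values leaves explainable variation in the error term. It also leaves any chance difference between the arms in lesion size inside the estimated treatment effect. With 48 patients per arm such differences can be noticeable.

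The article takes up covariate adjustment, but with tools that do not fit a responder outcome. ANOVA is set up there for continuous changes from baseline, and Kruskal-Wallis cannot adjust for covariates at all. An adjusted comparison of response rates would use data the trial already collects and would target the same quantity, the difference in response rates. What is at stake is some precision, not the validity of the primary test.

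**Working it through.** **Inputs from section 3.8.** n = 48 per arm; response 0.56 (ECT) and 0.36 (control); one-sided level 0.15; stated power 81%; stated achieved level 0.16.

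**Input not in the article.** R², the share of response variance explained by baseline lesion size and ECOG. It is assumed here to lie between 0 and 0.20.

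**Step 1: reproduce the plan's figures.** Take the pooled one-sided t-test on 0/1 responses (94 degrees of freedom), enumerate every pair of binomial outcomes, and sum the probabilities of the pairs that reject.
- Both arms at 0.36: rejection probability 0.158, which rounds to the stated 0.16.
- 0.56 against 0.36: rejection probability 81.05%, against the stated 81%.

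So the design figures are correct for the unadjusted test.

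**Step 2: a formula that can carry adjustment.** The normal approximation, with the pooled rate 0.46 under the null, is

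power = Φ{[0.20 − 1.036·√(2·0.46·0.54/m)] / √[(0.36·0.64 + 0.56·0.44)/m]}.

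With m = 48: (0.20 − 1.036 × 0.1017)/0.0997 = 0.949, so power is 82.9%. This is about 2 points above the exact value, so the gains matter here more than the levels.

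**Step 3: add adjustment.** Adjusting for covariates that explain a share R² multiplies the variance by about (1 − R²). That is equivalent to m = 48/(1 − R²). The last column is 48·(1 − R²), the number per arm with which an adjusted analysis would match the precision of 48 unadjusted.

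| Assumed R² | m | Power | Gain (points) | Equivalent n per arm |
|---|---|---|---|---|
| 0 | 48.0 | 82.9% | 0 | 48 |
| 0.02 | 49.0 | 83.4% | 0.5 | 47.0 |
| 0.05 | 50.5 | 84.2% | 1.3 | 45.6 |
| 0.10 | 53.3 | 85.5% | 2.6 | 43.2 |
| 0.20 | 60.0 | 88.2% | 5.4 | 38.4 |

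**Step 4: check by simulation.** 20,000 trials per setting, one standard-normal covariate in a logistic response model, marginal rates held at the plan's values. The unadjusted test is the pooled z-test; the adjusted test is a linear model with arm and covariate.

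| R² (approx.) | Power, unadjusted | Power, adjusted | Type I error, unadjusted | Type I error, adjusted |
|---|---|---|---|---|
| 0 | 81.6% | 82.3% | 0.164 | 0.155 |
| 0.04 | 82.0% | 83.9% | 0.164 | 0.154 |
| 0.10 | 81.5% | 84.8% | 0.161 | 0.150 |
| 0.19 | 81.8% | 88.1% | 0.166 | 0.151 |

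The first row shows about 0.7 points of gain with no prognostic value at all. That part comes from the change of test statistic and should be discounted in the other rows.

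**Step 5: size of chance imbalance.** The standard error of the between-arm difference in a baseline covariate is √(2/48) = 0.204 SD. Suppose the correlation with response is 0.3 (R² = 0.09) and take the response SD as about 0.49. A one-standard-error imbalance then moves the observed difference by 0.3 × 0.49 × 0.204 = 0.03, or 3 points. A two-standard-error imbalance moves it by 6 points, against a planned effect of 20. If the correlation is zero, both shifts are zero.

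**The case against.** **The planned test is valid and meets its target.** This stands. The 81% was computed for the unadjusted test and reproduces. A reader might infer that the trial is underpowered because it omits covariates, or that it loses a known amount of power. The article supports neither, since any gain depends on a prognostic strength it does not give.

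**Chance imbalance is not bias.** This stands too. A reader might infer that an imbalance in lesion size would distort the primary result. Under 1:1 randomisation it neither biases the unadjusted test nor inflates its type I error; it is part of the sampling variance already counted in the 81%. What remains is that an observed imbalance in a prognostic factor shifts the estimate in that one trial, which adjustment would reduce.

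**The evidence that lesion size is prognostic is thin.** This stands in part. RECIST response is judged relative to baseline size, so being its starting value does not make size a predictor. Electrode choice concerns the ECT arm only. Entry is limited to a single recurrence without nodal disease and to ECOG 0 to 2, which may narrow the range. This is why the low end of the R² range, including zero, has to be shown.

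**The covariate list may sit in the full protocol or the SAP.** This is a fair caution. Section 3.8 describes a power calculation and does not rule out an adjusted model, and the mention of local disease control in 3.9 leaves some doubt about how far the planned adjustment reaches. The point is therefore not that adjustment is missing. It is that the tests the article does name for response are unadjusted, and the adjustment methods it does name do not suit a binary outcome.

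**Conclusion.** The point holds as an optional improvement in efficiency, not as an error. The article names only unadjusted tests for objective response, while Visit 1 imaging and ECOG are available for an adjusted comparison.

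The gain is about 0.5 to 5 points of power at one-sided 0.15 if the covariates explain 2% to 20% of the variance in response, and essentially nil if they do not predict it. That range is an assumption, because the article gives no figure. The result also rests on the plan's own response rates and on one-sided 0.15 being the governing level.

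The last condition is unsettled, since 3.9 states p < 0.05. Read as two-sided 0.05, power with 48 per arm is about 50%, and adjustment with R² of 0.20 raises it only to about 60%. That conflict is a separate and more important matter, and covariate adjustment does not resolve it.

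**What to change.** In sections 3.8 and 3.9:

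1. Reconcile the level for the primary test (one-sided 0.15 against p < 0.05).
2. Make the primary analysis the covariate-adjusted difference in response rates: a model with arm, baseline target-lesion diameter (continuous) and ECOG status, standardised over all randomised patients, with a robust standard error, tested one-sided at the reconciled design level.
3. Take the diameter from the Visit 1 scan. The size entry in Table 2 is dated to the day of treatment, which is after randomisation.
4. Report the unadjusted difference as a sensitivity analysis.
5. Leave the sample size unchanged.

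**Cost.** Wording and one model run on data already collected, with no extra patients or visits. The covariates, their form and a rule for missing baseline values must be fixed before outcome data are seen. Missing values should be few, because measurable disease is an entry criterion.

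### The primary response comparison is sized at one-sided 0.15, but the analysis section calls differences significant only at p < 0.05, under which power is about 51% rather than 81%

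*Protocol article*

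**What the plan says.** **Section 3.8 (Description of Sample Size Calculation)** concerns the primary endpoint, objective response (CR + PR) by RECIST, under a superiority hypothesis:

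- Test: "The test statistic used is the one-sided T-test".
- Level: "The significance level of the test was targeted at 0.15", and "The significance level actually achieved by this design is 0.16".
- Size and power, for a planned difference of 20 points: "Group sample sizes of 48 in group one and 48 in group two achieve 81% power to detect a difference between the group proportions of" that size.
- Rates: the treatment arm "is assumed to be 0.36 under the null hypothesis and 0.56 under the alternative hypothesis". For control, "The proportion in group two (the control group) is 0.36".

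**Section 3.9 (Statistical Analysis)** says that objective response will be handled as a categorical variable. For such variables it says "For categorical variables, the chi square test for multiple comparisons will be used". The section ends with one general threshold: "Differences will be considered significant at *p* < 0.05". It does not mention 0.15, a one-sided test of response, or a separate rule for the primary endpoint. Where it states the sidedness of a test (the t-tests on changes from baseline), the test is two-sided.

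**The concern.** Both sections apply to the primary result, and they disagree on the test (t-test or chi-square), its direction (one-sided, or a test with no direction) and the level (0.15 or 0.05). Two things follow.

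- If section 3.9 governs, the power claimed in section 3.8 does not describe the analysis that will be done. The trial would enrol 96 patients with roughly even odds of detecting the effect it was designed for.
- If both sections stand, one data set can be positive under 3.8 and negative under 3.9. A reader cannot tell in advance which result counts as success, and the choice could be made once the data are known.

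A one-sided 0.15 is not itself the complaint. A relaxed level can be defended in a phase IIb trial, provided the analysis uses it.

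**Working it through.** **Inputs** (all from section 3.8 unless noted): n = 48 per arm; response 0.36 in control and 0.56 with ECT under the alternative; one-sided level 0.15. From section 3.9: chi-square test, p < 0.05. Section 3.9 does not give the sidedness of the threshold, so both readings are shown.

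**Method.** For every pair of responder counts (x_E, x_C) from 0 to 48, apply the test. Then sum the binomial probabilities of the pairs that reject. With p_E = x_E/48 and p_C = x_C/48:

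- t-test (94 df): t = (p_E − p_C) / √{[p_E(1 − p_E) + p_C(1 − p_C)]/47}. Reject one-sided at 0.15 if t ≥ 1.042.
- Chi-square, uncorrected: z = (p_E − p_C) / √{p̄(1 − p̄)·2/48}, where p̄ is the pooled proportion. Reject two-sided at 0.05 if |z| ≥ 1.960.

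**Step 1: reproduce the protocol's figures.** The one-sided t-test at 0.15 gives an achieved level of 0.158 (stated 0.16) and power of 81.05% (stated 81%). Both figures are right for their own inputs, so 0.15 is the level the design really used and not a misprint.

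**Step 2: power under the section 3.9 threshold, same n and rates.**

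| Rule for the primary endpoint | Power |
|---|---|
| One-sided t-test, 0.15 (section 3.8) | 81.0% |
| Chi-square, two-sided 0.05 | 51.2% |
| Chi-square with continuity correction, two-sided 0.05 | 42.8% |
| One-sided t-test, 0.05 | 61.5% |

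**Step 3: cross-check by normal approximation.** Power = Φ{(0.20 − z·SE₀)/SE₁}, where

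- SE₀ = √(2 × 0.46 × 0.54/48) = 0.1017
- SE₁ = √[(0.36 × 0.64 + 0.56 × 0.44)/48] = 0.0997

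Results:

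- One-sided 0.15 (z = 1.036): (0.20 − 0.1054)/0.0997 = 0.949, power 82.9%.
- Two-sided 0.05 (z = 1.960): (0.20 − 0.1994)/0.0997 = 0.006, power 50.2%.

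The second line shows why power is near one half: the smallest difference that is significant at two-sided 0.05 is about 0.199, almost exactly the planned 0.20.

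**Step 4: where the verdicts part.** Take 17/48 control responders (48 × 0.36 = 17.28).

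| ECT responders | Difference | Section 3.8: one-sided t-test p | Section 3.9: two-sided chi-square p |
|---|---|---|---|
| 22 | 10.4 points | 0.152 (negative) | 0.299 (negative) |
| 23 | 12.5 points | 0.109 (positive) | 0.214 (negative) |
| 26 | 18.8 points | 0.033 (positive) | 0.065 (negative) |
| 27 | 20.8 points | 0.020 (positive) | 0.041 (positive) |

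From 23 to 26 ECT responders the two sections give opposite answers.

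**Step 5: how often that happens.** Every result in favour of ECT that passes the chi-square rule also passes the 3.8 rule. Under the planned rates the chance of a split verdict is therefore 81.0% − 51.2% ≈ 30%. If both arms truly respond at 36%, it is 0.158 − 0.025 ≈ 13%.

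**Scale only, not a proposal.** By the normal approximation, 80% power at two-sided 0.05 would need about 97 per arm, and at one-sided 0.05 about 76 per arm, against 48 planned.

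**The case against.** The strongest reply is that section 3.8 already gives a complete and specific rule for the primary endpoint, with an achieved level that matches it. Section 3.9 never uses the word primary, and its p < 0.05 sentence comes straight after the paragraph on quality of life and pain. A specific rule may be read as overriding a general one, in which case 81% is correct and only a clarifying clause is missing. This may well be what was intended. It is not what is written: the sentence is general, and the same section explicitly covers objective response and sends categorical variables to a different test.

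A second reply is that the 51% assumes a two-sided 0.05, which the threshold sentence does not state, and that the only sidedness given for response is one-sided. That stands as a qualification. The two-sided reading is an assumption, supported by the non-directional chi-square test and by the other tests in section 3.9. Keeping the one-sided t-test and changing only the level gives about 61%, still some 20 points below the stated power.

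Third, the requirement of 27 against 17 responders should not be presented as a hurdle above the plan. The planned rates give 26.88 and 17.28 responders, so 27 against 17 is the planned effect in whole patients. The fair statement is that section 3.9 requires essentially the full planned effect to be observed, whereas section 3.8 requires 12.5 points.

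Finally, a fuller protocol or SAP may settle the matter. But this is not detail left out of a condensed article. The article fixes two incompatible rules, and a later document could agree with only one of them.

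**Conclusion.** The concern holds: the plan is wrong as written, because sections 3.8 and 3.9 set conflicting tests and levels for the primary endpoint. The 81% is correct for the one-sided 0.15 rule and only for that rule. If p < 0.05 governs the primary comparison, power is about 51% with the uncorrected two-sided chi-square test. It is 43% with continuity correction and 61% if 0.05 is read as a one-sided t-test. These figures assume 48 evaluable patients per arm and true rates of 36% and 56%, as in section 3.8. On the same rates, the two written rules (3.8, and the uncorrected two-sided chi-square) would disagree in about three trials in ten. This must be fixed before the primary analysis, because it determines what counts as a positive trial.

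**What to change.** In section 3.9, name one rule for the primary response comparison: the test, its sidedness and its level, identical to section 3.8 (one-sided, 0.15). State that two-sided p < 0.05 applies to the secondary analyses only. It would help readers to report the response difference with the two-sided 70% confidence interval that corresponds to a one-sided 0.15 test, together with a 95% interval, and to describe the result as a phase II screening decision. These reporting points are advisable, but the contradiction is removed without them.

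If 0.05 is really intended for the primary endpoint, correct section 3.8 instead: state the test and its sidedness, and give the power that 48 per arm provides (about 51% for the two-sided chi-square test, about 61% for the one-sided t-test).

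The cost is one or two sentences in section 3.9, or a less favourable power figure in section 3.8. Neither route adds patients.
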